## Abstract

**Introduction:**

This study aims to measure how transmission of SARS-CoV-2 occurs in communities and to identify conditions that lend to increased transmission focusing on congregate situations. We will measure SARS-CoV-2 in exhaled breath of asymptomatic and symptomatic persons using face mask sampling—a non-invasive method for SARS-CoV-2 detection in exhaled air. We aim to detect transmission clusters and identify risk factors for SARS-CoV-2 transmission in presymptomatic, asymptomatic and symptomatic individuals.

**Methods and analysis:**

In this observational prospective study with daily follow-up, index cases and their respective contacts are identified at each participating institution. Contact definitions are based on Centers for Disease Control and Prevention and local health department guidelines. Participants will wear masks with polyvinyl alcohol test strips adhered to the inside for 2 hours daily. The strips are applied to all masks used over at least 7 days. In addition, self-administered nasal swabs and (optional) finger prick blood samples are performed by participants. Samples are tested by standard PCR protocols and by novel antigen tests.

**Ethics and dissemination:**

This study was approved by the Colorado Multiple Institutional Review Board and the WHO Ethics Review Committee. From the data generated, we will analyse transmission clusters and risk factors for transmission of SARS-CoV-2 in congregate settings. The kinetics of asymptomatic transmission and the evaluation of non-invasive tools for detection of transmissibility are of crucial importance for the development of more targeted control interventions—and ultimately to assist with keeping congregate settings open that are essential for our social fabric.

**Trial registration number:**

ClinicalTrials.gov (#NCT05145803).

Strengths and limitations of this studyThe study employs a novel and non-invasive sampling device.Following index cases as well as their contacts prospectively enables us to study transmissibility.Results from the novel sampling device in the face masks are compared with standard nose swab sampling.The manuscript serves as a template for similar studies to be replicated.

## Introduction

There is an urgent need to better describe and analyse the transmission of SARS-CoV-2 in asymptomatic and presymptomatic (infected) individuals, especially regarding the heterogeneity of transmissibility (‘super-spreader events’), and within the context of congregate situations. An innovative tool with high sensitivity and minimal invasiveness is needed to obtain the necessary information to fill the current knowledge gaps.

A sizeable proportion of individuals infected with SARS-CoV-2 are asymptomatic. These individuals contribute to transmission and are also less likely to get tested. Asymptomatic SARS-CoV-2-infected individuals carry viral loads in conventional samples from the nasopharynx that are in the same range as those of symptomatic individuals, and a significant proportion of SARS-CoV-2 spread is due to asymptomatic individuals.^1–6^ An analytical model published by the Centers for Disease Control and Prevention (CDC) found that up to 59% of all transmissions likely resulted from asymptomatic transmission. The model further delineated that 35% of these 59% of infections resulted from those that eventually became symptomatic, while 24% remained asymptomatic.^7^ This study also found that the asymptomatic group positive for SARS-CoV-2 was only 25% less infectious compared with those that were symptomatic. This is in contrast to findings from systematic review studies focused on secondary attack rates where the authors concluded that secondar attack rates caused by asymptomatic individuals were only around 1% (and 7% in presymptomatic)^8^ or within household transmission around 3% (asymptomatic) and 20% (presymptomatic).^9^ Overall, few studies were designed specifically to study transmission in congregate situations, including index cases and their close contacts.

With the emergence of virus variants with the potential for greater infectivity, there is also a need to monitor viral variants in congregate situations among asymptomatic individuals, and to rapidly provide new information to public health authorities.^10^ This is especially true for breakthrough infections that require special monitoring regarding the details of the vaccines (type, intervals, etc) as well as the virus variants that caused the breakthrough infection.^11^

The reference method for detection of SARS-CoV-2 is the reverse transcriptase PCR, a technology that detects viral RNA from respiratory specimens (sputum or nasal swab) or from saliva. For diagnostic purposes, these samples are usually collected at a single point in time.

To study the dynamics of SARS-CoV-2 transmission over time, we investigate a non-invasive face mask sampling (FMS) method, where polyvinyl alcohol (PVA) strips are embedded in masks for the detection of SARS-CoV-2 in exhaled breath (figure 1). This enables us to extend the sampling interval over a time window (hours) and include different activities or risk factors such as singing, shouting, sneezing or coughing as part of the data collection process.

**Figure 1 F1:**
[figure not shown]
Two polyvinyl alcohol test strips adhered to the inside of a face mask. Photo credit: [name].

The overall aim of this study is to analyse transmission clusters of SARS-CoV-2 in communities and identify factors that may increase transmissibility, with a focus on congregate situations. We will compare the results from the FMS with the standard nasal swab. Within substudies, we are interested in better understanding antibody profiles and their correlation with symptom status and transmissibility, as well as the effect of different activities (such as singing or exercising) on test positivity in the masks. We also plan follow-up studies (which will need additional ethical approval) investigating long-term outcomes in the college student-age population regarding the incidence and the risk factors associated with long COVID-19. Details of the study objectives can be found in box 1.

Box 1ObjectivesStudy Identifier: clinicaltrial.gov identifier NCT05145803Objective 1: Identification of risk factors for, and rate of, infection in index cases and for transmission from index case to contacts.Objective 1.1: Describe demographics and evaluate risk factors for infection in index cases.Objective 1.2: Evaluate risk factors for transmission from index case to contacts (and their contacts), including viral load, clinical symptoms, vaccination status, activity and environmental metrics and immune response profiles (eg, neutralising antibodies, cytokine profiles—using a blood sample taken after recovery).Objective 1.3: Analyse the difference in the clinical status (symptomatic vs asymptomatic) for index cases as well as secondary cases by humoral and T-cell immune response profile (using the blood samples collected).Objective 1.4: Determine rate of and time to transmission, stratified by a variety of risk factors (including presence of clinical symptoms, activity and environmental metrics both in index cases and secondary contacts), analysing presymptomatic and asymptomatic exhalation of SARS-CoV-2 in contacts of index cases.Objective 2: In confirmed index cases and their contacts, quantify and determine the efficacy of the polyvinyl alcohol (PVA) test strip method for SARS-CoV-2 detection, comparing with the respective ‘reference standard’ (eg, nasal swab) collection method and correlating with the presence of antibodies.Objective 2.1: Assess the association between molecular detection by PVA test strip and molecular or antigen detection/quantification by initial reference diagnostic collection method.Objective 2.2: Assess the association between molecular detection by PVA test strip and molecular or antigen detection method (self-sampling) over the sampling/mask-wearing period.Objective 3: Due to the concern around emerging variants with higher transmissibility, carry out deep sequencing of PCR-positive samples (swabs as well as strips from masks) to derive the genotype of infecting virus.Objective 3.1: Share in timely fashion the results of the sequencing with the national/regional surveillance system.Objective 3.2: Assess the genetic similarities and differences of the SARS-CoV-2 variants by sequence comparison and by virological culture to assess cell-based infectivity of the strains.Objective 3.3: Determine the chain of transmission and relationship to clinical phenotype in the index case and contacts where viral RNA or culture permit.Objective 3.4: Analyse the difference in rate of transmission (see also objective 1) comparing different SARS-CoV-2 variants.

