
## Methods and analysis

### Study design

This is a prospective study with daily follow-up to capture early transmission in the presymptomatic phase. Index cases are identified by the routine testing system implemented at each participating institution and contacts of index cases are identified by the site-specific contact tracing system. The contact definition is based on CDC and the local health department guidelines (ie, individuals who are cohabitating or who were in close (<6 feet), extended (>15 min) contact with the index case and within 48 hours of diagnosis) and will be updated to reflect the most recent definition available. Study sites have an ongoing active case detection and contact tracing programme. Inclusion criteria and endpoints are described in box 2.

Box 2Key study design informationInclusion/exclusionInclusion criteriaIndex patients: Individuals aged≥18 years of any gender tested positive for SARS-CoV-2 by a molecular reference test (PCR test or antigen test).Contacts: Individuals aged≥18 years and known to be contacts of the index patients.Exclusion criteria: Age<18 years old, unable to wear a face mask due to underlying condition, unable to consent, pregnancy. In addition, signs of severe disease present at time of enrolment (eg, difficulty breathing, pain when breathing, tightness of chest or developing irregular heartbeat).EndpointsA. Outcome measure(s)Objective 1 outcomes: polyvinyl alcohol (PVA) strip positivity; nose swab test positivity.Objective 2 outcomes: PVA strip positivity and virus quantification (by PCR); nose swab test positivity; antigen test positivity; presence of antibodies in the blood.Objective 3 outcome: Deep sequencing of PCR-positive samples to derive the genotype of the infecting virus.

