### Schedule of wearing masks

Participants will be asked to wear a mask with two PVA test strips adhered to the inside surface for 2 hours per day. Index cases will complete 7 days of mask wearing and if they test positive by the end of the 7-day period, they will be asked to continue for another 7 days up to day 14. Contacts will complete 7 days of mask wearing as long as they test negative. If testing positive in the first 7 days, they will complete an additional 7 days of mask wearing starting with the day when they first test positive. If by the end of this period they still test positive, the duration will be extended by 2-day intervals with their permission until two consecutive masks wear dates test negative (figure 2). On completion of 2 hours of wear by the participant, the face masks will be placed in a sealed plastic bag, collected daily and brought into the laboratory where the PVA strips will be put into tubes with viral transport medium (VTM). The VTM tubes with the PVA strips will be eluted and tested by PCR.

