### Questionnaires

An electronic questionnaire is administered at the beginning of the mask-wearing period to collect basic demographics (age, gender) and to assess COVID-19 symptoms and activities (including the day when symptoms started). During the follow-up period, daily questionnaires are administered, and we have built in warning signs for potential severe COVID-19 that trigger an auto-alert, in which case we will proactively contact the participant and (a) ask the participant to stop wearing the masks and (b) advise the participant to seek medical care immediately. We also included an optional assessment of activities such as singing or exercising for index cases only (confirmed SARS-CoV-2 positive individuals) on 1 day using a separate second mask. In the future, the assessment of vital signs or specific symptoms could be added via wearable technologies or app-based recording (see, eg, https://www.hyfeapp.com/).

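### Index status follows order of detection, so the index-to-contact results of Objectives 1.2 and 1.4 can credit some transmissions to the recipient instead of the source

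*Protocol article*

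**What the plan says.** Box 1 of the protocol article frames the transmission questions as running outward from the index case. Objective 1.2 is to "Evaluate risk factors for transmission from index case to contacts (and their contacts), including viral load, clinical symptoms, vaccination status". Objective 1.4 asks for the rate of and time to transmission by clinical symptoms and other factors, and the Data analysis section adds the difference in rate by vaccination status.

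The labels come from the Study design section and Box 2:

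- "Index cases are identified by the routine testing system implemented at each participating institution". Besides the age limit and the exclusions, the criterion is having "tested positive for SARS-CoV-2 by a molecular reference test (PCR test or antigen test".
- A contact must be an adult "known to be contacts of the index patients". The contact definition covers cohabitants and people with close, prolonged contact "within 48 hours of diagnosis". It is tied to the index case's diagnosis, not to infection or symptom onset. No negative test at entry is required.
- Under Schedule of wearing masks, an early positive contact follows the same path as a later one: "If testing positive in the first 7 days, they will complete an additional 7 days of mask wearing".
- The Sample size section expects about 150 secondary cases among contacts, at 5% transmission from index case to contact.

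The Introduction says that asymptomatic infected people transmit and are less likely to be tested. From a cited model it reports up to 59% of transmission from people without symptoms, split as "35% of these 59% of infections resulted from those that eventually became symptomatic, while 24% remained asymptomatic". It also cites reviews with much lower secondary attack rates.

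**The concern.** Being diagnosed first is not the same as being infected first. By the article's own account, order of diagnosis depends on symptoms, which are one of the exposures under study. Suppose a symptom-free person infects someone who falls ill and is tested. The recipient becomes the index case. If the source is then enrolled as a contact and tests positive, it looks like a secondary case.

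In such a cluster, the symptoms, viral load and vaccination status analysed as the transmitter's belong to the recipient. Time to transmission is counted from the wrong person. A larger sample does not remove the error. Asymptomatic transmission is a main question of the study, and the article offers itself as a template, so the weakness could be repeated elsewhere.

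**Working it through.** **1. The plan's own figure.** Sample size section: 300 index cases, about 10 contacts each, 5% transmission.

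- Participants: 300 + 300 × 10 = 3300, as stated.
- Secondary cases: 300 × 10 × 0.05 = 150, as stated. All 150 are attributed to the index case.

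**2. Transmissions exposed to misattribution.** The Introduction's cited model gives 24% from never-symptomatic sources: 150 × 0.24 = 36. Let r be the share of these in which the source is diagnosed after a person it infected. The documents give no value for r, so a range is assumed; misattributed transmissions = 36 × r.

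| r (assumed) | misattributed, of 150 |
|---|---|
| 10% | 3.6 |
| 25% | 9 |
| 50% | 18 |
| 75% | 27 |

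These are misattributed transmissions, not all strictly reversed pairs. If one source infects several people, only the pair with the first-diagnosed recipient is reversed; the other recipients are wrongly linked to that recipient.

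**3. Low side of the cited evidence.** The Introduction also gives secondary attack rates from asymptomatic people of about 1% overall and 3% in households. Assume that 20% to 40% of true sources never have symptoms (not in the documents).

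- At 1%: 300 × 10 × 0.01 × (0.2 to 0.4) = 6 to 12 exposed transmissions, of which 10% to 75% is 0.6 to 9.
- At 3%: 18 to 36 exposed, so no more than in step 2.

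**4. Effect on the rate comparison (illustration only).** Assumptions: 10 contacts per source; overall rate 5%; a fraction f of 20% to 40% of sources never symptomatic; 70% of infected contacts symptomatic; true asymptomatic-to-symptomatic rate ratio 0.75 (the Introduction's 25% lower infectiousness). A cluster with a never-symptomatic source and at least one symptomatic recipient is reversed with probability q.

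Worked case, f = 0.3 and q = 0.5:

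- Rate per contact from symptomatic sources: 0.05 / (0.7 + 0.3 × 0.75) = 0.0541; from asymptomatic sources: 0.75 × 0.0541 = 0.0405.
- Reversed clusters: 300 × 0.3 × 0.5 × [1 − (1 − 0.7 × 0.0405)^10] = 11.3.
- Positives credited to asymptomatic index cases fall from 36.5 to 22.5; those credited to symptomatic index cases rise from 113.5 to 127.5.
- Observed rates: 0.0285 and 0.0576; ratio 0.495 instead of 0.75.

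| q (assumed) | observed ratio, true 0.75 | observed ratio, true 1.0 |
|---|---|---|
| 0 | 0.75 | 1.0 |
| 10% | 0.70 | 0.92–0.94 |
| 25% | 0.62–0.63 | 0.81–0.84 |
| 50% | 0.48–0.51 | 0.62–0.68 |
| 75% | 0.34–0.37 | 0.44–0.49 |

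The model lets reversal run one way only and enrols every overtaken source as a contact. It shows direction and sensitivity; it is not an estimate for this study.

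**5. Which analyses depend on direction.** The multilevel regression in Data analysis relates symptoms and behaviours to a person's own strip result, so it does not depend on who is called the index case. The index-to-contact rate, time to transmission, risk factors for transmission and rate by vaccination status do.

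**The case against.** The strongest reply is that this is a condensed article and that the handling of contacts already positive at entry belongs in the full protocol or analysis plan. No sentence in the article says that such a contact is scored as secondary, and the 150 is a planning count. That is fair as far as it goes. The point, however, rests on what the article does state: the two definitions, the direction of Objectives 1.2 and 1.4, and the count of secondary cases.

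Several limits stand:

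- A reader might infer that the direction of every pair is fixed. The documents do not support this. Objective 3.3 sets out to determine transmission chains, which is a partial safeguard. It depends on available material and is not tied to the Objective 1 analyses, and similar genomes show linkage without necessarily showing direction.
- A reader might infer that the bias runs strictly one way. Sites have active case detection, which can find a symptom-free recipient before a symptomatic source. The remark about less testing is general, not about these sites.
- A source outside the household whose contact fell outside the 48-hour window may never be enrolled as a contact.
- A reader might apply the 59% figure and the same assumed rates of 25% to 75%, giving 150 × 0.59 × r = 22 to 66 transmissions. Nothing supports those rates for presymptomatic sources, who later develop symptoms. The figure also ignores the lower attack rates cited beside it.
- It is tempting to say that onset and first-positive dates alone would orient the pairs. A never-symptomatic source has no onset date, and in this scenario its first positive comes after the index case's.

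**Conclusion.** The concern holds in a limited form. As defined, the index-to-contact results of Objectives 1.2 and 1.4, and the rate by vaccination status, can credit a transmission to its recipient, and the chance of this is linked to symptom status. The net effect is probably, but not certainly, to understate asymptomatic transmission.

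The size is unknown. The range of about 4 to 27 misattributed transmissions out of 150 rests on the cited 24% share and on assumed reversal of 10% to 75%; with the 1% attack rate it is about 1 to 9. The exploratory status of the study lowers the stakes but does not remove a foreseeable bias in one of its main comparisons.

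**What to change.** For Objectives 1.2, 1.4 and 3.3, do not treat every positive contact as secondary to the index case.

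1. Class a contact as co-primary or direction unresolved if the first study swab or strip is already positive, or if symptom onset is on or before the index case's. Use load trajectory and sequence linkage as supporting evidence.
2. Base the main transmission-rate, time-to-transmission and risk-factor analyses on contacts negative at their first study sample and not otherwise unresolved.
3. Repeat these analyses with unresolved pairs included as index to contact, and again with their direction reversed. Report asymptomatic transmission as a range across the three.

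The data are already planned: daily swabs and strips, and a questionnaire "to assess COVID-19 symptoms and activities (including the day when symptoms started". The cost is analysis wording and two repeat analyses, with no change to study procedures. The downside is that some pairs leave the main analysis. These will include true secondary cases infected before enrolment as well as true sources, which is why the repeat analyses are needed. A source that no longer tests positive at entry would still be missed.

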
## Methods and analysis

### Study design

This is a prospective study with daily follow-up to capture early transmission in the presymptomatic phase. Index cases are identified by the routine testing system implemented at each participating institution and contacts of index cases are identified by the site-specific contact tracing system. The contact definition is based on CDC and the local health department guidelines (ie, individuals who are cohabitating or who were in close (<6 feet), extended (>15 min) contact with the index case and within 48 hours of diagnosis) and will be updated to reflect the most recent definition available. Study sites have an ongoing active case detection and contact tracing programme. Inclusion criteria and endpoints are described in box 2.

Box 2Key study design informationInclusion/exclusionInclusion criteriaIndex patients: Individuals aged≥18 years of any gender tested positive for SARS-CoV-2 by a molecular reference test (PCR test or antigen test).Contacts: Individuals aged≥18 years and known to be contacts of the index patients.Exclusion criteria: Age<18 years old, unable to wear a face mask due to underlying condition, unable to consent, pregnancy. In addition, signs of severe disease present at time of enrolment (eg, difficulty breathing, pain when breathing, tightness of chest or developing irregular heartbeat).EndpointsA. Outcome measure(s)Objective 1 outcomes: polyvinyl alcohol (PVA) strip positivity; nose swab test positivity.Objective 2 outcomes: PVA strip positivity and virus quantification (by PCR); nose swab test positivity; antigen test positivity; presence of antibodies in the blood.Objective 3 outcome: Deep sequencing of PCR-positive samples to derive the genotype of the infecting virus.

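### The non-household contact window counts from the index case's diagnosis, so presymptomatic transmission from late-diagnosed symptomatic index cases is selectively under-captured

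*Protocol article*

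**What the plan says.** Study design in the protocol article states the purpose: "This is a prospective study with daily follow-up to capture early transmission in the presymptomatic phase". The Abstract adds the aim to "identify risk factors for SARS-CoV-2 transmission in presymptomatic, asymptomatic and symptomatic individuals".

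The same Study design section defines contacts as "individuals who are cohabitating or who were in close (<6 feet), extended (>15 min) contact with the index case", followed by the time limit "contact with the index case and within 48 hours of diagnosis". The definition rests on CDC and local health department guidance and "will be updated to reflect the most recent definition available". Contacts come from each site's own tracing system. On the source of index cases: "Index cases are identified by the routine testing system implemented at each participating institution".

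Box 2 admits any adult index case with a positive PCR or antigen test, subject to exclusions that do not concern time since onset. Objective 1.4 (Box 1) asks for the rate of and time to transmission by several factors, among them presence of symptoms in index cases and contacts. The baseline questionnaire covers symptoms, "including the day when symptoms started" (Questionnaires).

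**The concern.** The purpose depends on symptom onset, but the eligibility rule for non-household contacts depends on diagnosis. The two agree when the index case is diagnosed at or before onset and separate as the delay grows. Because Box 2 sets no limit on that delay, late-diagnosed index cases are eligible, and the people they met only before onset are not.

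The loss is selective. The excluded pairs are those whose exposure was unambiguously presymptomatic. Those retained from the same index cases are exposed after onset or across both phases. Presymptomatic estimates would then come mainly from index cases caught by screening or tested promptly, while symptomatic estimates would come from all. The Introduction motivates the study with conflicting published figures on transmission by the transmitter's symptom state, so this is a contrast that readers will look for.

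**Working it through.** **Inputs**
- Window: 48 hours, anchored to diagnosis (Study design).
- Cohabitation: an alternative to close, extended contact (Study design).
- Limit on time from onset to test: none stated (Box 2).
- 300 index cases at most, about 10 contacts each, 5% transmission (Sample size).
- Delay L, in days from onset to diagnosis: no distribution given.

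**1. The article's own figures.** Participants: 300 + 300 × 10 = 3300. Secondary cases: 300 × 10 × 0.05 = 150. Both reproduce.

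**2. Presymptomatic hours in the window.** Within the 48 hours before diagnosis, a symptomatic index case has max(0, 48 − 24 × L) presymptomatic hours.

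| L (days) | Anchored to diagnosis (h) | Anchored to onset (h) |
|---|---|---|
| 0 | 48 | 48 |
| 0.5 | 36 | 48 |
| 1 | 24 | 48 |
| 1.5 | 12 | 48 |
| 2 or more | 0 | 48 |

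If the 48 hours also run forward from diagnosis, an index case who already has symptoms adds only post-onset hours, so the result is unchanged.

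**3. Who is lost.** At L of 2 or more, a non-cohabiting person met only before onset does not qualify. Cohabitants do on the natural reading, since they form a separate limb, although the wording leaves unclear whether the 48-hour limit covers them too. A person met both before onset and inside the window also qualifies, but with exposure in both phases.

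**4. What remains.** Let s be the share of all index cases who are symptomatic and diagnosed 2 or more days after onset. The article does not give s, so the values below are assumptions for illustration. The other index cases number 300 × (1 − s), with 10 contacts each and 5% transmission.

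| s (assumed) | Other index cases | Contacts | Secondary cases |
|---|---|---|---|
| 20% | 240 | 2400 | 120 |
| 40% | 180 | 1800 | 90 |
| 60% | 120 | 1200 | 60 |
| 80% | 60 | 600 | 30 |

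For these index cases at least part of the window falls in a period without symptoms. Not every one of their pairs is a presymptomatic exposure, so the counts are upper limits on what they contribute.

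**5. Effect on a comparison.** For late-diagnosed index cases, dropping pre-onset pairs lowers the count of presymptomatic transmissions. Attack rates lose both numerator and denominator, so the error there depends on how early- and late-diagnosed index cases differ in infectiousness and contact pattern. The article gives nothing from which to compute either effect.

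**The case against.** A reader might infer that no presymptomatic close contact is eligible and that presymptomatic transmission cannot be estimated. The documents do not support that. Cohabitants and people met in both phases can qualify, and routine testing can find index cases before or soon after onset. Contacts are also followed daily through their own presymptomatic phase. Objective 1.4 places presymptomatic exhalation in the contacts, and objective 1.2 extends to the contacts' own contacts. All of this stands, and it limits the point to transmission from index cases. The daily follow-up does not fill that gap, because exhalation by a contact is not transmission from the index case. The second generation is only a partial remedy, since 300 + 3000 already uses the whole cap of 3300.

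A reader might also infer that pairs exposed before onset would be counted as symptomatic. Objective 1.4 does not say when symptom status is fixed, and such coding may be left to a fuller document. That misclassification is a risk to guard against, not a documented error.

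The definition follows guidance and may change. This does not remove the point: the article does not say that the anchor would change, and a later update would not by itself bring back contacts already left out.

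Finally, the study is exploratory, and the Data analysis section plans no explicit presymptomatic-versus-symptomatic comparison of transmission from index cases. The one rate comparison it names for objective 1 is by vaccination status. That lowers the stakes, but the Abstract's aim and objective 1.4 still invite the comparison.

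**Conclusion.** The point holds in limited form. Applied as written, the rule excludes non-cohabiting contacts exposed only before onset whenever a symptomatic index case is diagnosed 2 or more days after onset. Coverage of the 48 presymptomatic hours falls from 48 at no delay to 0 at two days. Presymptomatic transmission from index cases is selectively under-captured, though not impossible to estimate. Comparing it with symptomatic transmission across all index cases would be biased by an amount that the article does not allow to be computed, because neither the delay distribution nor the household share is given. The bias could be small if routine testing finds most cases early.

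This rests on two readings: that the 48-hour limit applies to close contacts and not to cohabitants, and that sites apply the definition as stated. The change is worth making because a stated rule is at fault and most of the repair is cheap.

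**What to change.** - Where site tracing permits, start the 48-hour look-back from the earlier of symptom onset and collection of the first positive specimen. State whether the 48-hour limit applies to cohabitants.
- Record the date or dates of exposure for each index–contact pair. For objectives 1.2 and 1.4, classify pairs by the index case's status at exposure (presymptomatic, symptomatic, never symptomatic), using the onset day already collected.
- Where tracing cannot be extended, or contacts are already enrolled, restrict estimates of presymptomatic transmission to index cases without symptoms at diagnosis or diagnosed less than 48 hours after onset.

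**Cost.** The second item needs one added field, and the third needs no new recruitment. The first depends on the sites, which run the tracing. With a delay of L days the look-back reaches L + 2 days before diagnosis, for example 5 days at L = 3. Recall is then longer, and some contacts start sampling later after exposure, when fewer may still be presymptomatic. The restricted analysis has fewer pairs. The cap of 3300 is unchanged.
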